**VISIT 0 // SELECTION**

| Patient initials |  |
| --- | --- |
| Patient identification code (n) |  |
| Date (DD-MM-YY) |  |

**SELECTION CRITERIA**

| Symptom-limited stress test without angina or electrical ischaemia (Y/N) |  |
| --- | --- |
| Informed consent (Y/N) |  |

**VISIT 1 // RANDOMISATION**

**PERSONAL DATA**

| Patient initials |  |
| --- | --- |
| Patient identification code (n) |  |
| Randomisation number (n) |  |
| Date (DD-MM-AA) |  |

**CLINICAL DATA**

| Unstable angina (Y/N) |  |
| --- | --- |
| NSTEACS (Y/N) |  |
| STEACS (Y/N) |  |
| Number of vessels (n) |  |
| Number of Stents (n) |  |
| Bypass Number (n) |  |
| Complete revascularisation (Y/N) |  |
| Diabetes mellitus (Y/N) |  |
| Arterial hypertension (Y/N) |  |
| Dyslipidaemia (Y/N) |  |
| Active smoking (Y/N) |  |
| Ex-smoker (Y/N) |  |
| Ejection fraction (%) |  |

**ADITIONAL MEDICATION**

| Beta-blockers (Y/N) |  |
| --- | --- |
| Calcium antagonists (Y/N) |  |
| Nitrates (Y/N) |  |
| Anti-aggregants (Y/N) |  |
| ACE inhibitors / ARBs (Y/N) |  |
| Lipid lowering agents (Y/N) |  |
| Others (Y/N) |  |

**PHYSICAL EXAMINATION**

| Height (cm) |  | Weight (Kg) |  |  |  |
| --- | --- | --- | --- | --- | --- |
| Heart Rate (bpm) |  | SBP (mmHg) |  | DBP (mmHg) |  |
| BMI (kg/m2) |  | Waist circumference (cm) |  | Hip circumference (cm) |  |

**STRESS TEST**

| VO2max |  |
| --- | --- |
| Effort time (min) |  |
| Maximum heart rate (Bpm) |  |
| Maximum blood pressure (mmHg) |  |
| METS (n) |  |
| ST descent (Y/N) |  |
| Angor (Y/N) |  |

**BLOOD TESTS**

| Glucose (mg/dl) |  | Creatinine (mg/dl) |  |
| --- | --- | --- | --- |
| Total cholesterol (mg/dl) |  | HDL cholesterol (mg/dl) |  |
| LDL cholesterol (mg/dl) |  | Triglycerides (mg/dl) |  |
| CRPus (mg/l) |  | HgA1c (%) |  |

**ARTERIAL STIFFNESS**

PWV (m/s)

**SURVEYS**

| IPAQ (n) |  |
| --- | --- |
| PREDIMED (n) |  |
| HAD ANXIETY (n) |  |
| HAD DEPRESSION (n) |  |
| EQ-5D |  |
| FAGERSTRÖM (n) |  |

**CLINICAL EVENTS**

| Consultation in the emergency department (Y/N) |  |
| --- | --- |
| Hospitalised (Y/N) |  |
| Revascularisation (Y/N) |  |

**SOCIO-OCCUPATIONAL SITUATION**

| Active worker until the event (Y/N) |  |
| --- | --- |

**VISIT 2 // MONTH 4**

**FILIATION DATA**

| Patient initials |  |
| --- | --- |
| Patient identification code (n) |  |
| Randomisation number (n) |  |
| Date (DD-MM-YY) |  |

**PHYSICAL EXAMINATION**

| Height (cm) |  | Weight (Kg) |  |  |  |
| --- | --- | --- | --- | --- | --- |
| Heart rate (bpm) |  | SBP (mmHg) |  | DBP (mmHg) |  |
| BMI (kg/m2) |  | Waist circumference (cm) |  | Hip circumference (cm) |  |

**BLOOD TESTS**

| Glucose (mg/dl) |  | Creatinine (mg/dl) |  |
| --- | --- | --- | --- |
| Total cholesterol (mg/dl) |  | HDL cholesterol (mg/dl) |  |
| LDL cholesterol (mg/dl) |  | Triglycerides (mg/dl) |  |
| CRPus (mg/l) |  | HgA1c (%) |  |

**CLINICAL EVENTS**

| Consultation in the emergency department (Y/N) |  |
| --- | --- |
| Hospitalised (Y/N) |  |
| Revascularisation (Y/N) |  |

**SOCIO-OCCUPATIONAL SITUATION**

| Active worker (Y/N) |  |
| --- | --- |
| Time to return to work after discharge (días) |  |

**VISIT 3 // MONTH 10**

**FILIATION DATA**

| Patient initials |  |
| --- | --- |
| Patient identification code (n) |  |
| Randomisation number (n) |  |
| Date (DD-MM-YY) |  |

**PHYSICAL EXAMINATION**

| Height (cm) |  | Weight (Kg) |  |  |  |
| --- | --- | --- | --- | --- | --- |
| Heart rate (bpm) |  | SBP (mmHg) |  | DBP (mmHg) |  |
| BMI (kg/m2) |  | Waist circumference (cm) |  | Hip circumference (cm) |  |

**BLOOD TESTS**

| Glucose (mg/dl) |  | Creatinine (mg/dl) |  |
| --- | --- | --- | --- |
| Total cholesterol (mg/dl) |  | HDL cholesterol (mg/dl) |  |
| LDL cholesterol (mg/dl) |  | Triglycerides (mg/dl) |  |
| CRPus (mg/l) |  | HgA1c (%) |  |

**STRESS TEST**

| VO2max |  |
| --- | --- |
| Effort time (min) |  |
| Maximum heart rate (Bpm) |  |
| Maximum blood pressure (mmHg) |  |
| METS (n) |  |
| ST descent (Y/N) |  |
| Angor (Y/N) |  |

**ARTERIAL STIFFNESS**

PWV (m/s)

**SURVEYS**

| IPAQ (n) |  |
| --- | --- |
| PREDIMED (n) |  |
| HAD ANXIETY (n) |  |
| HAD DEPRESSION (n) |  |
| EQ-5D |  |
| FAGERSTRÖM (n) |  |

**CLINICAL EVENTS**

| Consultation in the emergency department (Y/N) |  |
| --- | --- |
| Hospitalised (Y/N) |  |
| Revascularisation (Y/N) |  |

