## Secondary Objectives

Verify the improvement of the following parameters after the intervention:

A. Stress test:

● Demonstrate increase in VO2max.

● Demonstrate increase in exertion time.

● Demonstrate increase in workload.

● Decrease the presence of symptoms.

B. Analytical:

● Obtain improvement in lipid profile.

● Decrease in CRPus.

C. Lifestyle:

● Demonstrate increased adherence to Mediterranean diet.

● Demonstrate improved outcomes in psychological state.

● Demonstrate increased willingness to quit smoking and smoking cessation.

● Demonstrate a decrease in the sedentary lifestyle indicator.

● Demonstrate an earlier return to work.

D. Arterial stiffness

Improving carotid-femoral pulse wave velocity measurement

E. Socio-economic variables

To evaluate the cost per patient/month in the control cases of conventional rehabilitation and extended tele-rehabilitation intervention.

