# Sources of Information and Scope

The information sources for the present study are:

● Participating investigators.

● Data from the patient's medical history.

● Quality of life questionnaires (EQ-5D), Adherence to Mediterranean diet, physical activity (IPAQ), anxiety-depression questionnaire (HAD).

● Analytical data.

● Pulse wave velocity.

● Data derived from stress tests (treadmill).

● Socio-occupational data

The two rehabilitation protocols that are compared are those that have been adopted in each hospital centre. At La Fe hospital it has been in operation for years and at the Arnau de Vilanova hospital it is to be initiated with the present study. There are no additional tests except for the completion of the questionnaires mentioned above.

All necessary data will be collected in a data collection logbook (DCL).

Patients will be recruited from the Cardiology ward, in both hospitals.

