***CV Station 3***

WALK

DISTANCE

- Hypertension and cholesterol

- Coronary heart disease

- Cardiovascular drugs

- Heart disease and sex

- Diabetes

- Physical exercise

- Diet

- Tabaco

Intervention Group B.

The patients in Intervention Group B, included in the telerehabilitation program, will attend the hospital twice a week for 2 consecutive weeks, carrying out three sessions of physical exercise and four sessions of education on the same subjects as control group A. Subsequently, they will follow the guidelines programed in the ITS by carrying out their guided physical activities and adherence to the guidelines for management of their risk factors until the end of the study period. All the data generated are recorded in the professional application.

The program consists of two phases: an outpatient phase, in which the patient will attend the hospital 4 times during two weeks; and a second long-term phase of 10 months, where the patient will carry out the entire rehabilitation and prevention program with total independence.

Hospital phase: Starting on the first day, each individual in the patient team is provided with the ITS system described in the materials section. The patient is instructed to perform the programed physical activity and how to use the instrumentation, consisting of the application on the smartphone and the web connection to access the educational content and control of recommended hygienic and dietary measures, as well as monitoring of the pharmacological treatment. Ambulatory physical activity consists of walking at a sustained pace, until the effective heart rate equal to 75% of the maximum heart rate, obtained in the baseline stress test, is reached. The intensity of the exercise will be individually adapted according to the result of this same test. The hospital stay will be about two and a half hours, according to the following schedule:

1st session (Monday)

- Data collection: 60m

- Lecture: Explanation of the program and how the system works: 30m

- First exercise session: 60m

2nd session (Thursday)

- Clarification of doubts about how the system works: 30m

- Talk: Coronary heart disease and cardiovascular risk factors: 40m

- Second exercise session: 60m

3rd session (alternate weeks, Mondays) (12 patients)

- Talk: Anxiety and depression. Strategies to resolve conflicts: 45m.

- Talk: Sexuality and smoking: 45m

- Sketches humour: 30m

4th session (Thursdays)

- Talk: Hypertension and diabetes: 30m

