## Economic evaluation: cost-effectiveness analysis

The study includes a cost-effectiveness analysis to assess the costs and impact on health-related quality of life of the telerehabilitation intervention compared to in-hospital rehabilitation and the control group. The cost analysis will be carried out from the funder's perspective, including direct health care costs (pathology-related emergency visits, hospitalisations for the same cause, diagnostic and therapeutic tests such as revascularisations...) during follow-up. It will also include the costs derived from the intervention, which in the case of conventional rehabilitation, the programd schedule includes 16 rehabilitation visits, 8 rehabilitation sessions (with a physiotherapist, a nurse and a nursing assistant per session) and 8 educational talks. In the telerehabilitation group, the schedule includes 4 rehabilitation visits, 3 sessions (with a physiotherapist and a nurse) and 4 educational sessions. Unscheduled visits and sessions during the follow-up will also be included. The unit costs will be obtained from the Generalitat Valenciana catalogue.

Additionally, an analysis will be performed from a social perspective, including also indirect health care costs due to lost productivity of the patient (number of sick leaves and time to return to work after the event). Indirect costs will be reported by the patient in the follow-up data collection logbook. Effectiveness will be assessed by the physical activity performed by the patient, reported by the patient at the end of the follow-up, measured in METs-minutes/week.

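### The month-4 and month-10 logbook pages do not collect the quantities that the planned cost analysis needs

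*Protocol*

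**What the plan says.** Sections 1.8 and 4.2 of the protocol list a cost comparison among the secondary objectives: "To evaluate the cost per patient/month in the control cases of conventional rehabilitation and extended tele-rehabilitation intervention".

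Section 9.4 sets out the cost items. From the funder's perspective the analysis is described as "including direct health care costs (pathology-related emergency visits, hospitalisations for the same cause, diagnostic and therapeutic tests such as revascularisations...) during follow-up". It adds: "Unscheduled visits and sessions during the follow-up will also be included". The social perspective brings in lost productivity, made up of the number of sick leaves and the time to return to work. Its source is stated: "Indirect costs will be reported by the patient in the follow-up data collection logbook". Section 9.3 says that costs are built by quantifying resource use and applying official rates.

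On data capture, Section 5 says: "All necessary data will be collected in a data collection logbook (DCL)". Section 6.5 asks for three types of clinical event (emergency department, readmission, revascularisation) and gives no further detail.

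In Annex 1, the clinical-events block at Visit 2 (month 4) and Visit 3 (month 10) has three entries: "Consultation in the emergency department (Y/N)", "Hospitalised (Y/N)" and a matching yes/no entry for revascularisation. The socio-occupational block holds active worker (yes/no) and the days until return to work after discharge.

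**The concern.** A cost built from resource use needs quantities, and the follow-up pages mostly record only whether something happened. With a yes/no tick, repeated emergency visits or admissions within one period look like a single one. Without length of stay, an admission cannot be costed by bed-days. Without cause, the restriction to pathology-related visits and same-cause admissions cannot be applied. The pages also do not say whether the month-10 tick covers the time since month 4 or the whole follow-up, so an event ticked at month 4 could be ticked again.

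Two items are missing altogether. Section 9.4 needs the number of sick leaves and assigns indirect costs to the logbook, but the logbook has no such field. Unscheduled visits and sessions are to be costed and also have no field.

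At stake is a stated secondary objective. A later analysis plan can choose how to analyse costs, but it cannot recover patient-reported information that was never asked for.

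**Working it through.** The protocol states no cost figure, event rate or unit cost, so there is no figure to reproduce. The check is a comparison of the items in Section 9.4 with the month-4 and month-10 pages of Annex 1.

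| Item to be costed (Section 9.4) | Field at months 4 and 10 (Annex 1) | Sufficient? |
| --- | --- | --- |
| Pathology-related emergency visits | Yes/no | No: no count or cause |
| Same-cause hospitalisations | Yes/no | No: no count, cause or length of stay |
| Revascularisations | Yes/no | No: no count or date |
| Unscheduled visits and sessions | None | No |
| Number of sick leaves | None | No |
| Time to return to work | Days | Yes |

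Of these six items, one has a quantitative field, three have a yes/no field and two have none. Diagnostic tests other than revascularisation, which Section 9.4 also mentions, have no resource-use field either.

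**Illustration of the lost counts, with assumed rates.** Suppose the month-4 tick covers months 0 to 4 and the month-10 tick covers months 4 to 10. Each event type can then be recorded at most twice per patient. Let L be the mean number of events per patient over 10 months.

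- Poisson: expected number recorded = [1 − exp(−0.4L)] + [1 − exp(−0.6L)]. For L = 0.5 this is 0.1813 + 0.2592 = 0.4405, so the share missed is 1 − 0.4405/0.5 = 11.9%.
- Negative binomial with assumed k = 0.5: expected number recorded = [1 − (1 + 0.4L/k)^(−k)] + [1 − (1 + 0.6L/k)^(−k)]. For L = 0.5 this is 0.1548 + 0.2094 ≈ 0.3643, so the share missed is 27.1%.

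| Assumed L | Missed, Poisson | Missed, negative binomial (k = 0.5) |
| --- | --- | --- |
| 0.1 | 2.6% | 7.2% |
| 0.5 | 11.9% | 27.1% |
| 1 | 21.9% | 42.0% |
| 2 | 37.5% | 58.1% |

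The undercount depends entirely on L and k, which the protocol does not give. The missing cause and length of stay do not depend on the rate: they are absent from these fields even for a patient with a single event.

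**The case against.** The strongest reply is that the three ticks are not the only route to the data. Section 5 names the medical history as a source, Section 10 cross-checks the CRF against the clinical record, and Section 11 has the monitor verify that the two agree. A tick could therefore point to a record that holds dates, cause and stay. Section 8 also requires adverse reactions, defined broadly, to be entered in an adverse-reactions section of the logbook, with enough information on outcome, seriousness and causality; any admission counts as serious. That section is not among the Annex 1 pages, so those pages may not be the whole logbook. This much stands: admissions, and perhaps emergency use, may be recoverable. But no section names either route as the source for costing, and neither is said to supply the number of sick leaves or the unscheduled contacts.

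It also stands that the first absence from work is captured, as time to return to work. The gap concerns later sick leaves. The look-back period could be settled by a form instruction, since the two visits are dated separately.

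A reader might infer that the arms are captured unequally, because the telerehabilitation platform monitors patients and Section 6.4 says of that arm that "All the data generated are recorded in the professional application". The documents do not support this. Section 9.4 does not name the platform as a cost source, Section 6.5 collects clinical events on all patients at the same visits, and its intervention-only list contains no health-care contacts.

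A reader might also infer that the error is large. Participants are described as low risk in Section 13.2, and at an assumed 0.1 events per patient the illustrated undercount is only 2.6% to 7.2%.

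**Conclusion.** The point holds in a limited form. The number of later sick leaves and the unscheduled visits and sessions have no field and no stated source. For sick leave this contradicts Section 9.4, which sends indirect costs to the logbook. Emergency visits, admissions and revascularisations are recorded on the visit pages without count, cause, length of stay or look-back period, and no other source is designated for costing them. The secondary cost objective cannot be met from the form as printed.

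It would go too far to say that direct costs can never be calculated, since hospital records may fill that part. The size of the error in the cost comparison is unknown: it depends on event rates and unit costs that the protocol does not give, and the percentages above rest on assumed rates. No direction of bias between arms can be inferred. The primary comparison of METs-minutes/week is not affected. The conclusion assumes that the follow-up pages in Annex 1 are the ones to be used and that no separate economic form exists; the protocol mentions none.

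**What to change.** At months 4 and 10, with identical questions in both arms:

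- Replace each yes/no event tick with entries for the period since the last visit: number, date, related to the coronary event (yes/no) and, for admissions, length of stay.
- Add the number and days of sick leave.
- Add the number of unscheduled visits or sessions.

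In Section 9.4, state that direct-cost counts are taken from the hospital record in both arms. Section 10 already provides for cross-checking the CRF against the clinical record, so this builds on an existing step.

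The cost is a CRF revision and a few more minutes per visit. It needs no extra procedure and no extra patients.

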**SOCIO-OCCUPATIONAL SITUATION**

| Active worker (Y/N) |  |
| --- | --- |
| Time to return to work after discharge (días) |  |

